#### **12.5 Source data accessibility**

The IEC/IRB, the study monitor and QA auditors from Clinical Research Organisation and M/s Arjuna Natural Extract Limited will have the access to the raw data during inspection and audits.

#### **12.6 Data entry and verification**

After receiving the copy of CRFs, the data will be checked for inclusion and exclusion criteria and completeness. Major clarifications, if any, will be obtained from the Investigator.

#### **12.7 Archiving**

M/s Arjuna Natural Extract Limited will retain a representative sample of the study medication for a minimum period of 5 years after completion of the study. All the data generated during the conduct of study along with site master file and signed informed consent will be archived by the Investigator and a copy of all the documents

|                                                                                  |                                                                                                       |                                                              |
|----------------------------------------------------------------------------------|-------------------------------------------------------------------------------------------------------|--------------------------------------------------------------|
| [figure not shown] | Clinical trial to evaluate efficacy and safety of Amla Extract (AMX160) in patients with Dyslipidemia | Project No. AN-03ASE
0115H2-SYN02
Ver.01, Dt: 01-01-15 |
|----------------------------------------------------------------------------------|-------------------------------------------------------------------------------------------------------|--------------------------------------------------------------|

will be archived by the sponsor for a minimum period of 5 years after completion of the study.

## 12.8 Termination of study

The management of M/s Arjuna Natural Extract Limited, Kerala, India reserves the right to discontinue the study at any time. The study may be terminated by the IEC / IRB if there are major violations of ethical considerations or due to any serious adverse event. The reason for discontinuation of the study will be duly documented and the reason will be provided to all the Investigators involved in the study.

## 13 Test Product Management

### 13.1 Test Product description and packaging

Study medications consist of Amla Extract (AMX160) 500 mg capsules and matching placebo capsules. The test product would be packed in HDPE bottles each containing 66 capsules Amla Extract (AMX160) 500mg or matching placebo (56 capsules to be used during scheduled visit interval and 10 extra capsules to be used by patients if they fail to come on the scheduled dates). Each patient will be given one container each on visit 2 (Week 0), visit 3 (Week 4) and visit 4 (Week 8).

#### Composition of Test Products:

Each 500mg capsule contains: 500mg of Amla extract (AMX160)/ Placebo  
The test products will be manufactured by M/s Arjuna Natural Extracts Limited.

### 13.2 The precise dosing regimen

Patients will be instructed to take one Amla Extract (AMX160) 500 mg capsule or matching placebo capsule twice daily after meals as per the random allocation for the entire study duration of 12 weeks.

### 13.3 Method of packaging, labelling and blinding of Test Product

The study medication would be packed in a total of 3 containers each containing 66 capsules of Amla Extract (AMX160) 500 mg or matching placebo. To maintain blindness of study treatments, placebo capsules resembling in every manner to Amla Extract (AMX160) capsule will be used. The labels of the containers will contain Project No., Randomization No., Name of Test Product, Number of units of the study medication, Batch No, Manufacturing Date, Expiry Date/ Retest date, storage condition, name of manufacturer & sponsor and a statement "For Clinical Trial Use Only".

|                                                                                  |                                                                                                       |                                                              |
|----------------------------------------------------------------------------------|-------------------------------------------------------------------------------------------------------|--------------------------------------------------------------|
| [figure not shown] | Clinical trial to evaluate efficacy and safety of Amla Extract (AMX160) in patients with Dyslipidemia | Project No. AN-03ASE
0115H2-SYN02
Ver.01, Dt: 01-01-15 |
|----------------------------------------------------------------------------------|-------------------------------------------------------------------------------------------------------|--------------------------------------------------------------|

### **13.4 Method of treatment assignment and subject identification coding**

The subjects screened for eligibility for enrolment in the trial will be given a screening number. This would be a 10 digit no, first two digits would be site number followed by initials consisting of three digits, starting with 001 for each site. The screening number would be mentioned on the informed consent document of each patient. The patients found eligible for enrolment would be assigned a randomization number, which would consist of a seven digit numerical code, as per the randomization sheet provided to the investigator by the sponsor. Patients who, after consenting to the study, decide not to take part in the study or screen failure patients will retain their screening number, but will not be given randomization number. The next enrolled patient will be given the next randomization number. Each patient enrolled in the study will be given study medication as per the randomization number assigned to him/her. Randomization number given to any patient who discontinues the study or is lost to follow-up will not be allotted to any other subject during the study.

### **13.5 Storage conditions for Test Product**

All study supplies must be stored at room temperature, protected from light and separately from normal hospital / practice stocks in a secure locked facility accessible only to authorized personnel.

### **13.6 Test Product accountability**

The Investigator will confirm receipt of all the study test products in writing. A record of usage of supplies will be kept and the supplies, which are not used in the study, will be returned to the Sponsor after completion of the study. All courier receipts and logs will be maintained at the site for test product accountability. The study medications will be supplied to study patients under the responsibility of the investigator and the record of same must be maintained. All supplies must be accounted for at the end of the study period.

### **13.7 Procedures for handling unused Test Products**

Unused study test product supplies will be returned to M/s Arjuna Natural Extract Limited after completion of the study. Any discrepancy between the amounts dispensed and returned must be explained by investigator in the CRF.

## **14 Data Analysis**

|                                                                                   |                                                                                                       |                                                              |
|-----------------------------------------------------------------------------------|-------------------------------------------------------------------------------------------------------|--------------------------------------------------------------|
| [figure not shown] | Clinical trial to evaluate efficacy and safety of Amla Extract (AMX160) in patients with Dyslipidemia | Project No. AN-03ASE
0115H2-SYN02
Ver.01, Dt: 01-01-15 |
|-----------------------------------------------------------------------------------|-------------------------------------------------------------------------------------------------------|--------------------------------------------------------------|

#### 14.1 Sample size calculation

The sample size of 98 patients was calculated based on the following assumptions. Considering a mean reduction in TG between the group as 51 [29], the standard deviation as 76 [29] (effect Size 0.67 rounded to 0.7) with 5% alpha level (two sided) and power of 90%, at least 44 patients would be needed in each group. Assuming the dropout rate of 10% a total of 49 patients were enrolled in the study in each group. The enrolled patients would be assigned to either of the 2 treatment groups according to a centralized computer generated randomization plan in 1:1 ratio.

#### *Data Entry and Data Validation*

After checking and coding the completed CRFs, the data entry will be undertaken. A single time data entry with manual checking of the data will be done.

#### 14.2 Missing, Unused or Spurious Data

Clarifications, wherever possible, will be obtained from the respective Investigator for any missing data or for any illegible entry. Unused or spurious data will be kept in due confidentiality for a period of 5 years along with the other documents. Missing data shall not be imputed.

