## 6.3 Discontinued subjects

The investigator may withdraw a subject from the study if he/she meets any of the following withdrawal criteria:

1. Any patients / patient's legally acceptable representative who wishes to withdraw his / her consent for participation in the study
2. The subject suffers from significant intercurrent illness or undergoes surgery during the course of the study.
3. Any patient who requires/uses an unacceptable concomitant medication as per the Protocol
4. Failure to take 80% of the study medication during the study period

|                                                                                  |                                                                                                       |                                                              |
|----------------------------------------------------------------------------------|-------------------------------------------------------------------------------------------------------|--------------------------------------------------------------|
| [figure not shown] | Clinical trial to evaluate efficacy and safety of Amla Extract (AMX160) in patients with Dyslipidemia | Project No. AN-03ASE
0115H2-SYN02
Ver.01, Dt: 01-01-15 |
|----------------------------------------------------------------------------------|-------------------------------------------------------------------------------------------------------|--------------------------------------------------------------|

5. If it is felt in Investigator's / Medical Expert's opinion that it is not in the patients' best interest to continue.

The date the subject is withdrawn from the study and the reason thereof will be documented in the CRF. Withdrawn subjects will be considered for modified intention to treat efficacy analysis, if they have completed at least 1 visit post randomization (visit 3; week 4) with laboratory evaluation. Though every effort will be made to adhere to the schedule of visits, a window period of  $\pm 5$  days will be permitted for all the visits

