#### The primary efficacy endpoint would be:

1. Mean percent change in TG levels at the end of 12 weeks in the two groups

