not be included in the Per Protocol efficacy analysis while all the patients (including those with deviations and violations) will be considered for modified Intention To Treat efficacy analysis if they have completed visit 3 (week 4) with laboratory evaluation. All the subjects who have been dispensed study medication and have completed visit 3 (week 4) will be considered for safety evaluation.

Neither the investigator nor Arjuna Natural Extracts Limited will alter this study protocol. Amendments should be made only in exceptional cases once the study has started. Any change in the protocol should be approved by IEC / IRB, wherever necessary before implementation.

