#### 14.3 Statistical analysis

##### 14.4.1 Immunogenicity Population

##### Per Protocol Population

All the randomized patients who will complete the trial as per the defined protocol (including deviations) with both baseline and end of the study laboratory assessments will be considered in the Per Protocol analysis.

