##### Modified Intention to Treat Population (mITT)

All the randomized patients with baseline laboratory investigations and those who have completed at least one post randomization visit i.e visit 3 (week 4) with laboratory evaluation including patients with protocol violations will be considered in the mITT analysis.

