### **14.4.3 Data Analysis**

The data collected from the CRFs will be analysed for demographics, efficacy & safety. Data will be presented as mean  $\pm$  SD/SE or number (percentage). Descriptive statistics will be used for different variables at baseline. *P* value of  $< 0.05$  will be considered as statistically significant. Standard statistical tests will be used to analyse the data obtained. For efficacy analysis both, modified Intention To Treat (mITT) analysis and Per Protocol (PP) analysis will be done. The PP analysis will be considered as definitive, while the mITT analysis will be considered as supportive during the trial analysis.

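### Entry to the mITT set hangs on the week-4 visit, and no rule says how mITT patients without a week-12 triglyceride value enter the week-12 comparison

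*Protocol*

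**What the plan says.** Five rules in the protocol bear on this point.

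- **Endpoint.** Section 7.1 sets the primary endpoint as "Mean percent change in TG levels at the end of 12 weeks in the two groups". The schedule in section 7.3 also has TG measured at weeks 4 and 8.
- **Missing data.** Section 14.2: "Missing data shall not be imputed".
- **mITT membership.** This is worded three ways. Section 8.1 takes in all patients, violators included, "if they have completed visit 3 (week 4) with laboratory evaluation". Section 14.4.1 asks for baseline laboratory results and that patients have "completed at least one post randomization visit i.e visit 3 (week 4) with laboratory evaluation". Section 6.3 keeps withdrawn patients "if they have completed at least 1 visit post randomization (visit 3; week 4) with laboratory evaluation".
- **Per-protocol (PP) set.** Section 14.4.1 takes patients who complete the trial "with both baseline and end of the study laboratory assessments will be considered in the Per Protocol analysis".
- **Ranking.** Section 14.4.3: "The PP analysis will be considered as definitive, while the mITT analysis will be considered as supportive during the trial analysis". The only method it names is standard statistical tests.

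**The concern.** The mITT set is entered through week 4, the endpoint is read at week 12, and nothing in the protocol connects the two. This has two consequences.

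First, membership depends on attending one particular visit after randomisation. Someone who skips week 4 and returns for weeks 8 and 12 has a measured primary outcome that the mITT rule shuts out. The phrase about at least one visit in sections 6.3 and 14.4.1 suggests that a broader set was meant, but both sections then equate that visit with visit 3.

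Second, section 6.3 says that withdrawn patients with a week-4 sample count, yet no value is defined for them at week 12 and the protocol states no use for their week-4 and week-8 values. They can be members of the set and still contribute nothing to the primary comparison.

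What is at stake is the purpose of the mITT analysis. The definitive PP analysis is restricted to completers by definition, so mITT is the only planned efficacy analysis that could show whether losses after randomisation have shifted the result. One listed ground for withdrawal, "Failure to take 80% of the study medication during the study period", makes it plausible that losses are related to outcome.

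**Working it through.** **1. Who contributes a value.** The membership wording is applied below to five attendance patterns, with an ordinary two-group comparison of week-12 change.

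| Pattern after randomisation | In mITT as worded? | Week-12 TG? | Enters the comparison? |
|---|---|---|---|
| Attends weeks 4, 8 and 12 | yes | yes | yes |
| Protocol violator, attends weeks 4 and 12 | yes | yes | yes |
| Week-4 sample, then withdrawn | yes | no | no |
| Misses week 4, attends weeks 8 and 12 | no | yes | no |
| Withdrawn before week 4 | no | no | no |

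The comparison therefore runs on patients with both a week-4 and a week-12 sample. It differs from PP by keeping violators. It does not bring in the withdrawn patients that section 6.3 means to count.

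**2. The plan's own numbers.** Section 14.1 needs 44 per group and allows 10% dropout: 44 / (1 − 0.10) = 48.9, so 49 per group and 98 in all. This agrees with the protocol. In reverse, 49 × 0.90 = 44.1, so the trial is already sized for about 44 patients per arm with week-12 data. The question is bias, not numbers.

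**3. Patients lost through the visit-3 rule.** The protocol gives no rate. If 2%, 5% or 10% of the 44 missed visit 3 (an assumption), the rule removes 44 × 0.02 = 0.9, 44 × 0.05 = 2.2 or 44 × 0.10 = 4.4 patients per arm: about 1, 2 or 4.

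**4. Illustration of bias.** All inputs except the SD are assumed. Week-4 and week-12 changes are bivariate normal with SD 76 (section 14.1) and correlation 0.4, 0.6 or 0.8. There is no true effect. The log-odds of dropout change by 1.5 per SD of week-4 change. There are 200,000 simulated patients per arm per scenario. Error is the estimated active-minus-placebo difference, so a negative value flatters the active arm. The comparator is a regression of week 12 on week 4 within each arm, averaged over all patients. It stands in for a repeated-measures model and fills in no individual values.

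| Dropout, active / placebo | Who tends to drop out | Completer error at correlation 0.4 / 0.6 / 0.8 | Largest error using week 4 |
|---|---|---|---|
| 10% / 10% | poor early responders, both arms | −0.05 / 0.03 / 0.09 | 0.09 |
| 5% / 15% | poor early responders, both arms | 3.33 / 5.30 / 6.72 | 0.23 |
| 20% / 5% | poor early responders, both arms | −4.48 / −7.42 / −9.35 | 0.48 |
| 10% / 10% | poor responders on active, good responders on placebo | −7.01 / −10.93 / −14.66 | 0.50 |

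Against the planned difference of 51, the non-zero errors run from 3.33 / 51 = 6.5% to 14.66 / 51 = 29%, in either direction. Dropout here depends only on an observed value, which is the situation in which using week 4 works. The unit is that of the 51 and 76 in section 14.1, not percent change.

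**The case against.** The strongest reply is that section 14.2 bars imputation and nothing more. A likelihood-based repeated-measures model uses weeks 4 and 8 without imputing, section 14.4.3 leaves the method open, and a statistical analysis plan that is not shown may specify it. That stands. A reader might infer that the no-imputation rule by itself makes mITT a completer analysis. It does so only under an ordinary two-group test. No choice of model, however, restores patients whom the visit-3 wording keeps out of the set.

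Other stronger readings are tempting, and the protocol does not support them:

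- *Non-adherent and withdrawn patients vanish from both efficacy analyses.* Violators stay in mITT, withdrawal under section 6.3 is at the investigator's discretion, and non-adherent patients who reach week 12 still count. Section 10.2.2 also calls for a final evaluation at discontinuation, although it gives that evaluation no role in the analysis.
- *A patient who misses week 4 is lost from PP too.* Section 8.1 lists a missed procedure as a deviation, which PP tolerates, and failure to report within 7 days as a violation, which it does not. Which one covers a missed visit is unsettled.
- *The ATP-goal proportion is taken among completers.* Sections 7.1 and 14 give no denominator.

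The missed-visit case may also be rare. Visit 3 is a dispensing visit. A patient who skips it without make-up supply receives at most 2 × 66 = 132 of 168 scheduled capsules (78.6%), and the unscheduled visit form provides for a make-up visit. Low intake is no reason for exclusion from a set that keeps violators by design, so this limits how often the problem arises and does not remove it.

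**Conclusion.** The point holds in a limited form and should be fixed. It is not a fatal flaw. Two things rest on the protocol's own text: the visit-3 condition excludes patients with an observed primary outcome and sits awkwardly beside the at-least-one-visit wording, and withdrawn patients are counted in mITT with no stated way to contribute at week 12. Unless a repeated-measures analysis is used, mITT then reduces to patients with week-12 data, violators included, and says little about the effect of dropout on the definitive PP result.

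No single figure for bias is defensible. It is about zero if both arms lose patients in the same way. In the assumed patterns where they differ it reached about 3 to 15, against 51. A reader might instead take 10% × 51 = 5.1 as the overstatement. That assumes no benefit in any active-arm dropout, and a repeated-measures model would not remove it if dropout were unrelated to the observed values. Only a sensitivity analysis addresses that case.

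Because mITT is ranked as supportive, repairing it leaves the headline analysis unchanged. The ranking of PP as definitive is the weightier matter.

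**What to change.** 1. Use one mITT definition in sections 6.3, 8.1 and 14.4.1: all randomised patients with a baseline and any post-baseline TG, with no visit-3 condition.
2. State that the week-12 treatment contrast comes from a repeated-measures model on the scheduled week 4, 8 and 12 values, with baseline as covariate. This needs no imputation and is compatible with section 14.2.
3. State how patients without week-12 data count in the ATP-goal proportion.
4. Add one sensitivity analysis that assumes no benefit after dropout. If it assigns values to individual patients, limit the no-imputation sentence in section 14.2 to the main analysis.

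The cost is a wording change and slightly more analysis work. No visits or samples are added, because the week-4 and week-8 TG values are already scheduled.

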#### 14.3 Statistical analysis

##### 14.4.1 Immunogenicity Population

##### Per Protocol Population

All the randomized patients who will complete the trial as per the defined protocol (including deviations) with both baseline and end of the study laboratory assessments will be considered in the Per Protocol analysis.

##### Modified Intention to Treat Population (mITT)

All the randomized patients with baseline laboratory investigations and those who have completed at least one post randomization visit i.e visit 3 (week 4) with laboratory evaluation including patients with protocol violations will be considered in the mITT analysis.

##### 14.4.2 Safety Population

Safety population will include all the randomized patients who have been dispensed study medication and have completed at least one post randomization visit i.e. visit 3 (week 4) will be considered for safety evaluation.

|                                                                                   |                                                                                                       |                                                              |
|-----------------------------------------------------------------------------------|-------------------------------------------------------------------------------------------------------|--------------------------------------------------------------|
| [figure not shown] | Clinical trial to evaluate efficacy and safety of Amla Extract (AMX160) in patients with Dyslipidemia | Project No. AN-03ASE
0115H2-SYN02
Ver.01, Dt: 01-01-15 |
|-----------------------------------------------------------------------------------|-------------------------------------------------------------------------------------------------------|--------------------------------------------------------------|

